##### Per-protocol analysis

In addition to the ITT analysis, a PP analysis will be conducted to assess the intervention’s effects on those who adhered to the protocol. This analysis will provide insight into the maximum impact of the intervention when implemented without deviations.

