**Methods:**

In this parallel, two-arm superiority randomized controlled trial, participants with physician-confirmed uncomplicated UTI who have filled an oral antibiotic prescription will be recruited from six tertiary care hospitals in Khyber Pakhtunkhwa, Pakistan. The participants will be randomized in a 1:1 manner to receive either the VISTA intervention or standard care. The VISTA intervention was developed based on nudge theory, guided by the Taxonomy of Choice Architecture framework, and complemented by the MINDSPACE (messenger, incentives, norms, defaults, salience, priming, affect, commitments, and ego) framework. It was developed and validated through a Delphi method, assessing expert feedback, and refined based on a patient understanding study. The intervention sticker uses contrasting colors—red (non-adherence: bacteria evolving into “superbugs”) and green (adherence: antibiotics fully eradicating bacteria)—to communicate the consequences of incomplete versus complete adherence. The primary outcome is adherence, measured by pill count at the initial follow-up. Secondary outcomes include UTI recurrence, knowledge, and attitudes regarding antibiotic adherence. Analysis will follow both intention-to-treat and per-protocol principles.

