### Blinding

The study participants and site staff delivering the intervention will remain unblinded due to the nature of the behavioral intervention. The individual blinded to the intervention assignment will carry out the data analysis using the neutrally labeled data set, such as “group A” and “group B.” To ensure consistent and objective measurement of the outcomes, site staff will receive training to rigorously follow the protocol, and regular monitoring and audits will be conducted to ensure compliance. The physician responsible for patient diagnosis and confirming UTI recurrence will remain blinded to the intervention assignment.

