### Outcomes

#### Primary outcome

The primary outcome is antibiotic adherence, measured by tracking the pill count at the end of the prescribed antibiotic treatment. This will be expressed as a proportion (number of pills taken/total prescribed) and as a categorical variable (adhered vs. not adhered). Adherence is defined as taking ≥ 90% of the prescribed antibiotic course [32]. This will be assessed during a follow-up visit to the hospital or a home visit.

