#### Follow-up data

At the follow-up stage, pill counts will measure adherence, and structured questionnaires will be administered to assess changes in knowledge and attitudes regarding antibiotic use. Then, the next follow-up will be done after 1 month, 3 months, and 6 months. At each follow-up, either at the hospital or home visit, the pill count will be performed by the trained data collectors. Returned blister packs will be checked against prescription records. Any discrepancies between the baseline dispensed quantity and the physical count will be documented in site monitoring logs and reviewed by the site supervisor. If packaging is not returned, adherence via pill count will be coded “not verifiable” and treated as missing for the primary pill-count outcome. The details are given in Fig. 8. The overall schedule of enrollment, interventions, and assessments is illustrated in Fig. 9.

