#### Intention-to-treat (ITT) and per-protocol (PP) analysis

##### ITT analysis

The primary analysis will follow the intention-to-treat (ITT) principle and include all randomized participants. We will handle participants with lost to follow-up, missing outcomes, and covariate data using multiple imputations by chained equations (MICE) under a missing-at-random (MAR) assumption [42, 43]. The imputation model will include the primary outcome, baseline covariates predictive of outcome and missingness (age, sex, MPI category, baseline knowledge, and attitude scores). We will generate at least m = max (20, % missing × 1) imputations, fit the planned analysis model within each imputed dataset, and combine estimates using Rubin’s rules [44]. The participants who formally withdraw consent will be excluded from the analysis.

To assess robustness to departures from MAR, we will conduct sensitivity analyses: (1) a complete-case analysis; (2) pattern-mixture/delta-adjustment sensitivity analyses that impose plausible shifts (delta) to imputed outcomes under missing-not-at-random (MNAR) scenarios; and (3) a conservative worst-case/best-case bounds analysis for the primary binary outcome. Results from sensitivity analyses will be reported alongside the primary multiple imputation results and used to assess the robustness of conclusions regarding treatment effect.

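### The per-protocol comparison cannot show the sticker's maximum impact: it is open to selection bias of unknown direction and is not an upper bound

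*Protocol article*

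**What the plan says.** The Per-protocol analysis section names the population only as the participants who kept to the protocol: "a PP analysis will be conducted to assess the intervention’s effects on those who adhered to the protocol". It then gives the result an interpretation: "This analysis will provide insight into the maximum impact of the intervention when implemented without deviations". The article adds no caveat and describes no adjustment for selection after randomisation.

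Four other places bear on the point:

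- **ITT analysis:** "The primary analysis will follow the intention-to-treat (ITT) principle and include all randomized participants". Multiple imputation, delta-adjustment and best-case/worst-case bounds go with it.
- **Abstract, Methods:** both analyses are named without ranking: "Analysis will follow both intention-to-treat and per-protocol principles".
- **Primary outcome:** the endpoint is itself a form of adherence: "Adherence is defined as taking ≥ 90% of the prescribed antibiotic course".
- **Blinding:** "The study participants and site staff delivering the intervention will remain unblinded due to the nature of the behavioral intervention".

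**The concern.** A per-protocol set is formed from what happens after randomisation. If the reasons for leaving the set are related to pill-taking and differ between arms, the remaining groups are no longer comparable and the contrast mixes the sticker's effect with selection.

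This trial gives reasons to expect that. Participants and delivering staff know the allocation. Failure to deliver the sticker is a deviation that belongs to the intervention arm; the Delivery section allows for dispensing at outside pharmacies and drug stores, and the Discussion lists fidelity across sites as a challenge. Under Follow-up data, a pack that is not returned leaves the outcome missing: "If packaging is not returned, adherence via pill count will be coded “not verifiable” and treated as missing for the primary pill-count outcome". Returning a pack and attending for the count may well go with taking the pills.

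At stake is how a secondary result is read. A figure labelled in advance as the most the sticker can achieve could be quoted that way when it may lie above or below the true effect.

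**Working it through.** **The plan's own figures.** The per-protocol section states no number. The adherence rates come from the sample-size paragraph: 64.3% (intervention) and 48.3% (control), a difference of 16.0 points. The odds ratio is (0.643/0.357)/(0.483/0.517) = 1.93. Cohen's h is 0.324, which agrees with the stated 0.32; h of 0.324 and 0.32 give 150 and 154 per group, on either side of the stated 152. The rates are therefore a sound starting point. All exclusion and retention rates below are assumptions.

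**Illustration 1: exclusions in one arm, no true effect.** Let a fraction d of one arm be excluded, with adherence p_d among those excluded. Adherence in the rest of that arm is (0.483 − d × p_d)/(1 − d).

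| d | p_d | Calculation | Adherence in the set | Shift |
|---|---|---|---|---|
| 0.10 | 0.30 | 0.453/0.90 | 50.3% | 2.0 points |
| 0.15 | 0.30 | 0.438/0.85 | 51.5% | 3.2 points |
| 0.15 | 0.20 | 0.453/0.85 | 53.3% | 5.0 points |

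If the exclusions are in the intervention arm, the shift appears as a benefit (+2.0 to +5.0). If they are in the control arm, it appears as a harm (−2.0 to −5.0).

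**Illustration 2: retention that depends on the outcome.** Let r1 and r0 be the chances that an adherent and a non-adherent patient stay in the set. Adherence in the set is p·r1/(p·r1 + (1 − p)·r0), so the odds in that arm are multiplied by r1/r0.

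| Retention, intervention (r1/r0) | Retention, control (r1/r0) | No true effect | True effect +16.0 points (OR 1.93) |
|---|---|---|---|
| 95%/75% | 85%/85% | +5.9 points, OR 1.27 | +21.2 points, OR 2.44 |
| 95%/60% | 85%/85% | +11.4 points, OR 1.58 | +25.7 points, OR 3.05 |
| 85%/85% | 95%/75% | −5.9 points, OR 0.79 | +10.1 points, OR 1.52 |
| 85%/85% | 95%/60% | −11.4 points, OR 0.63 | +4.6 points, OR 1.22 |
| 95%/75% | 95%/75% | 0 points, OR 1.00 | +15.3 points, OR 1.93 |

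For the last entry of the second row: 0.643 × 0.95/(0.643 × 0.95 + 0.357 × 0.60) = 0.611/0.825 = 74.0%, and 74.0 − 48.3 = 25.7 points. In the fifth row the factor r1/r0 cancels between arms, so the odds ratio does not move.

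In the third and fourth rows a true 16-point effect gives a per-protocol estimate below 16 points. An estimate that can fall below the true effect is not a maximum.

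**Comparison with an estimate that keeps randomisation.** The complier-average estimate is the ITT risk difference divided by the between-arm difference in sticker receipt. With receipt of 85% against 0% (assumed), a null ITT difference gives 0/0.85 = 0, and a 16.0-point ITT difference gives 16.0/0.85 = 18.8 points. With receipt of 98% against 0% (assumed), it gives 16.0/0.98 = 16.3 points, close to ITT.

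**The case against.** The strongest case on the other side is that a supplementary per-protocol analysis beside a primary ITT analysis is conventional, that the detailed definition of the set commonly sits in the SAP or full protocol, and that the text promises only insight. All of this is fair. The lack of listed criteria in the article is not the fault here. What remains is the interpretation that the article does state, and no later definition of the set would make the estimate a maximum.

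A reader might infer more than the documents support:

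- **That the bias must inflate the effect, because controls have nothing to deviate from.** Either arm can become ineligible, be hospitalised or transferred, miss a visit or fail to return a pack, and a control could receive a sticker by mistake. Nor does the article say that a missed sticker goes with poor pill-taking. The direction is unknown.
- **That the set selects on the outcome, because "effects on those who adhered to the protocol" means taking the pills.** The sentence that follows speaks of implementation, and antibiotic adherence is defined separately. The ambiguity is a risk to close, not an established error.
- **That per-protocol and ITT have equal standing.** Only the abstract leaves them unranked; the body ranks them.
- **That the policy brief will rest on the per-protocol figure.** The Dissemination section does not say so.

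**Conclusion.** The point holds in a limited form. The per-protocol comparison is liable to selection bias of unknown direction, so the protocol should not present it as the intervention's maximum impact or as the effect without deviations.

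Under the assumed exclusions, the spurious difference with no true effect is 2.0 to 5.0 points in either direction. It reaches about 11 points under the more selective retention scenarios, and a true 16-point effect could appear as anything from 4.6 to 25.7 points. These figures show what is possible. They are not forecasts, since the documents give no deviation or retention rates, and identical selection in both arms would leave the odds ratio untouched. The comparison is therefore open to bias rather than certain to be biased.

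The trial's main conclusion rests on ITT and is not threatened. This is a cheap correction that is worth making.

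**What to change.** 1. Delete the maximum-impact interpretation from the Per-protocol analysis section.
2. Label the analysis supportive and open to selection bias. This applies even if the set is defined by eligibility and confirmed sticker delivery, because excluding undelivered intervention patients is also selection after randomisation.
3. State that the set is never defined by the pill count or by any other measure of pill-taking.
4. In the abstract, say that ITT is primary, as the body already does.
5. If the effect under full delivery is of interest, report a complier-average estimate with randomisation as the instrument: the ITT risk difference divided by the between-arm difference in sticker receipt. State its exclusion restriction, that allocation affects pill-taking only through receipt of the sticker. This deserves comment because staff and participants are unblinded. State also that the estimate applies to those who receive the sticker when allocated to it.

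**Cost.** Items 1 to 4 are a few sentences. Item 5 needs sticker delivery recorded for each participant, a single field in the data-collection form, and a short extra analysis. Its interval is somewhat wider: dividing by 0.85, for example, stretches the ITT interval by about 1/0.85 = 1.18 times. If delivery is nearly complete, the estimate will be close to ITT and adds little.

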### Ethical considerations

#### Informed consent

Informed consent will be obtained from each participant by a trained data collector at each hospital site, ensuring that they receive a clear explanation of the study’s purpose (improving antibiotic adherence through VISTA intervention), procedures (randomization, intervention delivery, follow-up visits for pill counts, and questionnaire survey), and potential risks and benefits. Participants will be explicitly assured that their participation is entirely voluntary, and they retain the right to withdraw from the study at any time without penalty or impact on their medical care. Additionally, the consent process will describe data anonymization measures, such as replacing personal identifiers with unique codes, and confidentiality safeguards, including secure storage of data and restricted access to authorized study personnel only.

#### Ethical approval

The Ethics Committee of the Department of Pharmacy Practice, Bahauddin Zakariya University, Multan (Approval No. BZU-FOPDPP-2466) and Saidu Group of Teaching Hospitals, Swat (Approval No. 1401/03) reviewed and approved the study.

Any important protocol amendments, such as changes to eligibility criteria, outcomes, or analyses, will be reviewed and approved by the relevant ethics committees, updated in ClinicalTrials.gov, and communicated to all investigators and participating sites.

#### Study registration

The trial was registered with ClinicalTrials.gov on March 3, 2025, with trial ID: NCT06885658 (https://register.clinicaltrials.gov/prs/beta/records).

### Qualitative analysis

A qualitative study will examine the perceived mechanisms through which the VISTA intervention influences antibiotic adherence, focusing on participants’ experiences, behavioral pathways, and contextual factors.

A qualitative descriptive approach will be employed. Semi-structured interviews will be conducted with purposefully selected patients. Sample size will be determined based on thematic saturation. Participants will be selected from the intervention group for post-intervention delivery and adherence assessment. Patients who completed the follow-up for adherence measurement and expressed willingness to participate in the study will be included. Semi-structured interviews will follow an interview guide based on the Theoretical Domains Framework (TDF) [33]. TDF will assist in identifying the behavioral barriers and enablers affecting antibiotic adherence. This allows the interview guide to explore the multifaceted factors influencing adherence. The interviews will be conducted in the local language (Urdu/Pashto), audio-recorded, and transcribed into English.

The qualitative data will be analyzed using thematic analysis. The transcripts will be coded using TDF domains to identify patterns. Emergent themes will be integrated with TDF themes. This sub-study will provide actionable insights into how and why the intervention works, ensuring its theoretical coherence and contextual relevance. Findings will guide refinements for scalability in low-resource settings and inform future implementation strategies.

## Discussion

This study aims to investigate the efficacy of visual storytelling as an intervention to enhance antibiotic adherence among patients diagnosed with UTIs. The potential of visual storytelling to impact health behavior is based on its capability to bridge the gaps between knowledge and action.

Storytelling can enhance engagement and promote health behavior change. Nudge theory explains that the way choices are presented significantly nudges behavior and can lead to desired behavioral actions [45]. Narrative theory explains that stories can influence attitudes by encouraging emotional transportation, where individuals become mentally absorbed in a narrative, resulting in changes in belief and behavior [15]. Visual storytelling adds an extra layer, amplifying this effect by incorporating visual elements that appeal to both cognitive and emotional processing, thereby improving the retention and recall of health messages and behaviors. In the context of antibiotic adherence, visual storytelling aims to address cognitive and emotional barriers that typically hinder adherence, such as lack of understanding, forgetfulness, and resistance to taking medication as prescribed. By presenting the outcomes of choices offered for antibiotic adherence, this intervention will encourage patients to recognize the importance of completing their antibiotic course, thereby reducing the risk of antibiotic resistance. VISTA intervention aligns well with goals to improve antibiotic adherence in UTI patients through patient-centered engagement. For instance, a recent review showed that storytelling improved self-management and peer support in chronic disease patients by fostering self-efficacy [16]. Similarly, digital storytelling has been shown to improve emotional engagement and understanding among immigrants and the refugee population, which can motivate patients to adhere to treatment plans [46]. Furthermore, combining multimedia in visual storytelling improves comprehension of complex health information [47], supporting the use of this approach to emphasize the importance of completing antibiotic courses and mitigating non-compliance. However, in Pakistan, in contexts like Pakistan, where nearly half of the population lacks mobile access [23], the feasibility of digital storytelling intervention may be limited. To overcome this barrier while preserving the benefits of storytelling, we have developed a sticker-based VISTA intervention to improve patients’ adherence to antibiotics.

The primary outcome of the trial will be adherence to antibiotic regimens among UTI patients, as measured by pill counts. Secondary outcomes will include improvements in patient knowledge regarding antibiotic use, changes in attitudes toward antibiotic resistance, and increased patient confidence in managing their health. As demonstrated in other health-related storytelling interventions, visual stories that emphasize the emotional and practical aspects of behavior change, such as the potential consequences of not completing antibiotic courses, are more likely to lead to sustained changes in behavior [48]. The intervention will also aim to increase patient self-efficacy, which is often a predictor of health behavior change. By providing patients with the outcomes of their choices, we anticipate an increase in their ability to adhere to prescribed regimens.

The use of VISTA intervention to improve antibiotic adherence is a novel approach, bridging behavioral science and clinical practice. While storytelling has proven effective in other health domains, such as vaccination promotion and chronic disease management [16, 47, 48], its application to antibiotic adherence is underexplored. This tool could be easily adopted by policymakers into national antimicrobial stewardship programs, while clinicians could incorporate it into patient counseling. Empirical validation of its efficacy within the UTI cohort will demonstrate its translational potential, enabling adaptation to other prevalent infections, such as respiratory tract infections. By facilitating a transformative approach to antimicrobial stewardship, this intervention aligns with global priorities for combating antibiotic resistance while addressing critical gaps in low-resource healthcare systems.

This study presents numerous methodological and practical strengths. Foremost, its RCT design guarantees a rigorous assessment of the intervention’s efficacy, thereby minimizing bias through the processes of randomization and the blinding of outcome assessors. The incorporation of nudge theory provides robust theoretical support, which enhances the intervention’s capacity to foster significant behavior modification. Moreover, the development of the intervention entailed a structured two-step methodology, which included expert consensus via the Delphi technique and soliciting patient feedback. This comprehensive approach ensures cultural relevance, clarity, and practicality for implementation in real-world settings. The employment of objective adherence measures, such as pill counts, alongside blind physician evaluations of UTI recurrence, further fortifies the validity of the findings. Lastly, the intervention’s cost-effective, sticker-based format renders it scalable and adaptable to a range of healthcare environments, aligning with the WHO’s priorities regarding antimicrobial stewardship in resource-constrained regions [49].

While this study addresses critical gaps in antibiotic adherence research, certain limitations merit consideration. First, pill counts, though objective, may not fully capture intentional non-adherence; for example, skipped doses despite retained pills. However, the analysis of the UTI recurrence can indirectly assess the effectiveness of the intervention. Second, the regional focus on tertiary hospitals in Pakistan may limit generalizability to other populations. However, the inclusion of culturally tailored content, refined through Delphi consensus and patient feedback, enhances relevance to similar low-resource settings. Third, external factors such as medication access or healthcare provider communication could influence adherence. While these variables are challenging to control in real-world trials, the feasibility study explicitly evaluates logistical barriers (e.g., recruitment rates, sticker delivery fidelity) to optimize implementation. Fourth, the 6-month follow-up period may not fully capture long-term adherence patterns or ABR outcomes. Finally, there is potential social desirability bias in self-reported knowledge and attitude responses.

Implementation challenges may arise related to the development, printing, and distribution logistics of intervention materials, variability in staff training and engagement, and maintaining intervention fidelity across diverse study sites. Ensuring consistent supervision, particularly in resource-limited hospital settings, will be essential. Addressing these operational factors early will be crucial for the sustainability, scalability, and policy translation of the VISTA intervention.

If effective, the VISTA intervention can be integrated into provincial and AMR programs through collaboration with the Ministry of National Health Services, Regulations and Coordination (MoNHSRC) and provincial health departments. Integration into community pharmacy and primary-care education platforms, supported by existing AMR stewardship initiatives, would allow wider adoption.

